In the context of responsiveness to exercise, a study from our laboratory suggested that health-related benefits may be modality specific. Spence et al. (2011) utilised two dichotomous exercise intervention modalities, endurance (END) and resistance (RES) training, which induce distinct haemodynamic and physiological stimuli for physiological adaptation. We found that cardiac adaptation differed between modalities [[6], [7], [8], [9]]. However, subjects in this study were randomised to parallel groups and completed only one exercise intervention/modality. It is therefore possible that the distinct responses to alternate exercise modalities that we observed might have been biased by the randomisation process. A within-subject cross-over design is a more appropriate approach to address the question of whether the response to distinct exercise modalities differs within individuals. Using this design, we can also determine whether individuals demonstrate concordant or discordant responses to distinct forms of training (i.e. whether low-response to one form of exercise training necessarily implies low-response to all modalities). This has implications for the optimisation of exercise prescription in humans, whereby switching to an alternate form of exercise could “rescue” subjects who otherwise may not have benefited.

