##### Cogstate

2.7.9.1

A battery of reliable and well-validated cognitive tests was administered to encompass a range of cognitive domains [50]. These tests were conducted by a trained researcher and test results were analysed by the same individual, blinded to testing order. The following tests were conducted:•Detection test- A 3 min test which provides a measure of psychomotor function reaction time and is assessed by speed of performance.•Identification test- A 3 min test which measures attention and choice reaction time via speed of performance.•Maze learning test- A 7 min test that measures executive function via total number of errors made during the task.•International shopping list test- A 5 min test that measures verbal learning and episodic memory. This is done by measuring the total number of correct answers in remembering the list on three consecutive trials, at a single session.•Two back test- A 4 min test which measures working memory via on-line monitoring, updating and manipulation of remembered information. This test is scored using accuracy of performance.•Set-shifting test- This test measures executive function or the ability to display flexibility using total number of errors in 7 min.•Modified chase task- This 4 min test measures executive function or response inhibition using speed of performance.•SF-12 health survey- This 12-item questionnaire takes approximately 2 min to complete and assesses health and well-being. Specific outcome measures include physical and social functioning, role limitations due to emotional problems, mental health, energy/vitality, pain, and general health perception.•PSQI- This 5 min survey provides a measure of the participants current sleep behaviour.•DASS21- This 3 min survey provides information on measures of depression, anxiety and stress.

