##### Endothelium-dependent vasodilation: flow-mediated dilation

2.7.10.2

To assess endothelium-dependent vasodilation of the brachial and femoral arteries, the flow-mediated dilation (FMD) technique was used (Supplementary Fig. 3), described in more detail elsewhere [56]. The reliability of FMD tested ~7 days apart in healthy subjects has a high correlation (r = 0.82) [58]. In summary, a rapid inflation-deflation pneumatic cuff (D.E. Hokanson Inc., Bellevue, WA, USA) was wrapped around the left forearm, 2 cm distal to the olecranon process. A second larger cuff was positioned on the upper left thigh ~15 cm distal of the inguinal ligament, or ~5 cm proximal to the patella and patella tendon. The arterial-lumen interface was optimised for longitudinal B-mode images of the brachial and femoral arteries. Continuous Doppler pulse wave velocity of each artery was simultaneously obtained (by two expert vascular sonographers) using the lowest possible isonation angle (60°). Dynamic range and Doppler gain settings were consistent between machines, and specifications were replicated for each individual on repeat visits. The left arm was placed at the height of the heart in approximately 80⸰ abduction from the body. The arm was supported underneath the muscles and the hand slightly pronated in a relaxed position for the participant. The brachial artery was scanned in the middle or upper third of the arm, depending on positioning of the brachial artery bifurcation. The brachial artery was also scanned either through the biceps brachii or between the biceps and triceps brachii muscles, depending on which gave a cleaner image for analysis for that particular participant. The femoral artery was assessed in the proximal third of the thigh, at least 5 cm distal from the bifurcation, with the left leg in slight (<5°) lateral rotation. These anatomical specifications were noted at the initial testing session and replicated at the repeated visits.

A baseline scan was recorded for a period of 1 min to assess resting blood vessel diameter, shear rate and blood flow velocity. Both blood flow occluding cuffs were rapidly inflated to a suprasystolic pressure of 220 mmHg for 5 min. Recording resumed 30s prior to cuff deflation so that it wasn't missed and continued for 3 min post-deflation [59]. Peak artery FMD (absolute and %), shear stress, time to peak and artery diameter pre-post cuff were analysed as previously described [56,58,59].

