
## Planned statistical analysis

3

Statistical analyses are to be performed with SPSS 20.0 (IBM Australia Ltd, New South Wales, Australia) and STATA 11 software (StataCorp, College Station, Texas). All data will be reported as group means with confidence intervals, with default statistical significance assumed at *P* < 0.05. Cross-sectional results for each outcome measure refer to baseline entry (week 0) data. Response to training data is post minus pre for END and RES training. Normality of groups (MZ and DZ) will be assessed via Shapiro-Wilk test of normality where normality of spread is assumed at *P* > 0.05. Between-group (MZ vs DZ) differences will be assessed with the conservative non-parametric Mann-Whitney *U* test and regression models including the single covariate zygosity (MZ/DZ), fitted using a generalised estimating equation (GEE) approach to account for correlation of twins within-pairs. The effect of the exercise interventions on each outcome measure will be assessed using a linear mixed models approach.

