The primary objective of the current study is to estimate the MZ and DZ correlations and the variance components A, C and E for each outcome measure cross-sectionally, and in response to exercise training (END and RES). In STATA mixed models effects will calculate intraclass correlation coefficients (r) for MZ and DZ twin pairs. Covariates to be adjusted for (e.g. sex, fat-free mass, VO_2max_, baseline data) will depend on the primary outcome measure. The subsequent rMZ and rDZ, and their respective P-values and 95% confidence intervals will be presented. Differences between intraclass correlations (rMZ vs rDZ) will be assessed using the likelihood-ratio test in STATA to compare mixed effects models constraining covariances for MZ and DZ pairs to be equal with models allowing different covariances for MZ and DZ pairs [69]. If the model allowing different MZ and DZ covariances are significantly better, and rMZ are significantly different to rDZ, A, C and E will then be calculated from the estimates of the DZ covariance and the additional MZ covariance, and confidence intervals for A, C and E will be estimated using the delta method. When rMZ and rDZ are not significantly different then a single model that includes all twin pairs but constrains the covariance to be equal for MZ and DZ pairs will be used in STATA to calculate C and E components only, and their respective 95% confidence intervals. An additional model which estimates covariance for MZ twins but fixes the DZ covariance to be zero will test if the estimated correlations suggest that the equal environments assumption has been violated.

Secondary objectives of this study will be addressed using the individual change with training (END and RES) results for each outcome measure. Response rates for each modality can be derived as a percentage of positive responses (>0) and compared against one another by a Z-test. Concordances can be derived as the percentage of individuals who positively respond to both exercise training modalities (Supplementary Fig. 5). In a similar way to the correlation analyses, within-twin pair concordances for MZ and DZ can be derived for each exercise intervention and compared to each other.

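### A responder rule of any change above zero sets no direction of benefit and no margin for measurement error, so the response, concordance and rescue percentages cannot be told from noise

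*Protocol article*

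**What the plan says.** Section 3 (Planned statistical analysis) of the protocol article fixes the change score: "Response to training data is post minus pre for END and RES training". The secondary objectives are then to be met from individual changes on all outcomes, by two rules. For response: "Response rates for each modality can be derived as a percentage of positive responses (>0", the two rates then being set against each other with a Z-test. For concordance: "Concordances can be derived as the percentage of individuals who positively respond to both exercise training modalities (Supplementary Fig. 5"; that supplementary figure is not among the material shown. Within-pair concordances for MZ and DZ twins are to be formed along the same lines.

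The Introduction sets the question these percentages serve, namely "whether low-response to one form of exercise training necessarily implies low-response to all modalities", and suggests that a change of modality might rescue a low responder. The Summary (section 4) frames the aim around people who get no substantive benefit from one mode.

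The outcomes include several where lower is better. The maze test, for example, "measures executive function via total number of errors made during the task". Section 2.7 also quotes repeatability for a number of measurements. For flow-mediated dilation it says: "The reliability of FMD tested ~7 days apart in healthy subjects has a high correlation (r = 0.82".

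**The concern.** One rule is applied to outcomes that differ in direction and in precision.

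- **Direction.** For blood pressure, LDL, hs-CRP, percent fat, pulse wave velocity and error totals, benefit is a fall. Post minus pre with a cut above zero scores the people who got worse as responders.
- **Noise.** A cut at zero leaves no room for test-retest error. People with no true change are split about evenly into responders and non-responders. People who all gain the same amount are split too, which looks like individual variation.
- **Rescue.** The named concordance counts only people positive on both modes. The plan names neither the share low on both nor the share low on one mode who respond to the other, and it makes no comparison with chance.

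At stake is the claim that switching modality helps low responders. Measurement error alone can produce the pattern that would support it.

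**Working it through.** The article states no expected response rate, concordance or rescue rate, so there is no figure of its own to reproduce. The check works from the rule.

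**Inputs.** The rule: change above 0 (section 3). VO2max technical error: 2.4% (section 2.7.2). Middle cerebral artery velocity, day-to-day coefficient of variation: 4.5% (section 2.7.9). FMD test-retest r = 0.82 (section 2.7.10.2). Assumptions: errors are normal, and are independent between the END and RES changes, which come from separate visits (weeks 0 and 12, weeks 24 and 36).

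**Direction.** If 80% improve through a fall (assumed), 1 − 0.80 = 20% have a change above zero, and 20% is the rate the literal rule reports.

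**Error in a change.** SD of change from error alone = √2 × test error.

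- VO2max: 1.414 × 2.4% = 3.4%.
- Middle cerebral artery velocity: 1.414 × 4.5% = 6.4%.
- FMD: √(2 × (1 − 0.82)) = 0.60 between-person SD, if the cited correlation is read as an intraclass correlation that holds in this sample.

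**What error alone produces.** Let everyone have the same true change d on both modes, in units of the SD of change error. The response rate is p = Φ(d). Responding to both is p², to one only 2p(1 − p), to neither (1 − p)². Apparent rescue is (p − p²)/(1 − p) = p.

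| d | Respond to each mode | Both | One only | Neither | Apparent rescue |
|---|---|---|---|---|---|
| 0 | 50% | 25% | 50% | 25% | 50% |
| 0.524 | 70% | 49% | 42% | 9% | 70% |
| 1 | 84% | 71% | 27% | 2.5% | 84% |

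No row contains any true difference between people.

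**Rescue from the planned percentages.** With response rates pE and pR and both-respond share p11, rescue by RES = (pR − p11)/(1 − pE), and both low = 1 − pE − pR + p11. Take p11 = 49%:

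- pE = pR = 70%: (0.70 − 0.49)/0.30 = 70%.
- pE = pR = 60%: (0.60 − 0.49)/0.40 = 27.5%.

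Concordance alone does not fix the rescue rate; together with the two response rates it does.

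**Effect of an error-based cut.** 1.96 × √2 × test error gives 6.7% for VO2max and 12.5% for middle cerebral artery velocity. At zero true change, false response falls from 50% to 2.5%, and false concordance from 25% to 0.025² = 0.06%. A looser cut of twice the test error gives 1 − Φ(2/√2) = 7.9% false response.

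**The case against.** **Positive may mean beneficial.** The Introduction speaks of beneficial responses, the supplementary figure may set out the classification, the wording is permissive, and sign coding per outcome is often left to a fuller plan. This stands in part: reversal is the literal reading and not proven intent. But the bracketed cut above zero, applied to post minus pre, gives the word an arithmetic meaning, and the text shown has no sign convention.

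**A reader might infer that the plan cannot answer the rescue question.** The documents do not support that. Both response rates and the both-respond share are planned. Section 2.6 requires 80% adherence across both interventions for a pair to enter the final analyses, so the percentages should come from the same people. The full table, the rescue rate, chance agreement and kappa then follow by arithmetic. What remains is that the plan does not name these quantities, and that the zero cut makes them uninterpretable.

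**A reader might infer that the heritability results or hypothesis 4 fall with the rule.** They do not. The A/C/E components and the linear mixed models of intervention effect use continuous data. Agreement within MZ and DZ pairs is tested on continuous change through rMZ versus rDZ with a likelihood-ratio test. Only the added dichotomous pair concordances inherit the problem.

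**A threshold cannot come from the cited figures for every outcome.** This stands. FMD, GTN response and cardiac MRI have only correlations, and 1RM an ICC and a correlation; these give no error in outcome units without an SD. No error figure is stated for biochemistry, blood pressure, pulse wave velocity or the cognitive tests. For LV mass, wall thickness or resting artery diameter in healthy young adults, the article states no beneficial direction.

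**Conclusion.** The point holds for the response-rate comparison, objective 2b, hypothesis 3 and the rescue conclusion. Under the zero cut, error alone gives 50% responders, 25% concordant and 50% apparently rescued when nothing changes. It gives 84%, 71% and 84% when everyone gains one SD of change error. These figures rest on normal errors that are independent between the two modes, and on the same true change for everyone. The reversal, 80% improved reported as 20%, is an assumed example and depends on the literal reading. The rule also sits badly with the article's own interest in substantive benefit, which a change just above zero does not show.

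This is a fault in a secondary analysis that can be mended without new data and leaves the primary objective untouched. It should be fixed, but it does not undermine the trial.

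**What to change.** 1. State the beneficial direction for each outcome and score response in that direction. Analyse outcomes with no clear beneficial direction as continuous change only.
2. Use an error-based threshold where an error in outcome units is cited (VO2max, middle cerebral artery velocity). Elsewhere use one only if it can be derived from a stated SD, with the stated assumption that the cited reliability transfers to this sample. Show the zero cut as a sensitivity analysis. For VO2max, settle which error figure is meant: 0.15 L/min and 2.4% agree only at 0.15/0.024 = 6.25 L/min.
3. Report the full END-by-RES table for each dichotomised outcome, with the rescue rate in each direction, the both-low rate and kappa. Beside it, give the correlation between continuous END and RES changes from a model that allows for twin pairs. Error pulls that correlation towards zero but, if independent between the modes, does not create agreement.

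The cost is some extra analysis and response rates that look lower. A strict cut also misses real responders: a true 10% gain in middle cerebral artery velocity (illustrative) clears the 12.5% cut with probability 1 − Φ((12.47 − 10)/6.36) = 1 − Φ(0.39) = 35%. That is why the continuous correlation should stand beside the table.

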### Washout, carryover and order effects

3.1

Analysis of the effectiveness of the washout period, carryover effects and the order effect of the exercise interventions will be assessed in SPSS and STATA. To assess the effectiveness of the washout period, the presence of carryover effects, or order effect of the exercise interventions, we will initially calculate and present summary statistics comparing groups according to the order of first administration for each intervention. The entire time series of data, including time-points following the washout, will also be presented. As a first descriptive step, group means for these comparisons will be compared using *t*-test, assuming data is normally distributed. If not, non-parametric alternatives will be used. In this way, the magnitude of change for those completing END 1st versus 2nd, and RES 1st versus 2nd, will be presented and compared. This approach will be followed by mixed models, where an ‘order’ variable (eg endurance first, endurance second) will be included in models as a factor in interactions. The length of our washout period was based on our previous findings and we do not anticipate persistent effects for the variables we will measure in this study, but any significant effects will be addressed by inclusion in our statistical models (mixed models ANOVA) of baseline values as covariates. The dependence of twins within a pair will be accounted for by fitting regression models adjusting for correlations within-twin pairs using the GEE approach in STATA to test whether time period (week 0 vs week 24) or order (END/RES vs RES/END) are associated with the outcomes.

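### The Z-test for endurance v resistance response rates ignores both the cross-over and the twin pairs, so its true error rate is not 5% and its direction cannot be known in advance

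*Protocol article*

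**What the plan says.** Section 3 (Planned statistical analysis) addresses the secondary objectives through individual change with training. The operative sentence takes, for each modality, the percentage of changes above zero as its response rate, and has the two rates "compared against one another by a Z-test". It mentions neither pairing within a person nor clustering within a twin pair.

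The design creates both. The Introduction justifies the trial by its cross-over: "A within-subject cross-over design is a more appropriate approach to address the question" of whether responses differ within individuals. Section 2.4 randomises the twin pair and has both twins train in the same modality at the same time. Table 1 gives 31 MZ and 14 DZ pairs, so 62 + 28 = 90 people.

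Elsewhere the article does allow for twin dependence. For zygosity contrasts section 3 says "Between-group (MZ vs DZ) differences will be assessed with the conservative non-parametric Mann-Whitney *U* test", but the same sentence adds regression models "fitted using a generalised estimating equation (GEE) approach to account for correlation of twins within-pairs". In section 3.1, for washout and order effects, "group means for these comparisons will be compared using" t-tests as a first descriptive step, followed by mixed models and GEE. The response-rate comparison has no such companion.

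**The concern.** A two-proportion Z-test takes the variance of the difference as the sum of two independent binomial variances. Two features of the trial break this, in opposite directions. If a person who responds to END also tends to respond to RES, the difference in rates varies less than the test assumes, and the test is too strict. If twins respond alike, the difference varies more, and the test is too liberal. The net error depends on how strongly END and RES responses correlate within a person. That is close to what secondary objective (b), on concordance between modalities, sets out to learn, so the sponsor cannot know beforehand which way the P-values err.

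The comparison bears on secondary objective (a), whether response differs by modality, and on the Introduction's idea that switching modality might rescue low responders. If responses are largely modality-specific, as hypothesis 2 expects, the test leans towards false differences. If they are strongly concordant, it gives away the precision that the cross-over was chosen to provide.

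**Working it through.** **Inputs from the article.** 31 MZ and 14 DZ pairs (Table 1). Alpha 0.05 (section 3; taken here as two-sided). Within-pair correlations (section 3.2): 0.74/0.37 for FMD training response in an earlier twin study, 0.80/0.30 as planning values, and 0.60/0.38 for FMD cross-sectionally.

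**Assumptions.** A response rate of 0.7 in both modalities, prompted by the Introduction's figure of up to 30% low responders (0.5 was also run). The END-RES correlation within a person, rw, is not in the article and was varied from -0.2 to 0.7. The correlation between one twin's END response and the co-twin's RES response was set to r × rw. Responses are a normal latent variable, cut to give the response rate.

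**Calibration.** The article gives no operating figure for this test beyond nominal 5%. With all correlations zero, 20,000 simulated trials of the pooled Z-test (90 v 90) reject in 4.9%, as they should.

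**Z-test under the design.** Simulated type I error at response rate 0.7:

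| rw | no twin correlation | twins 0.74/0.37 | twins 0.80/0.30 |
|---|---|---|---|
| -0.2 | 6.3% | 12.6% | 12.9% |
| 0 | 4.9% | 9.6% | 10.3% |
| 0.2 | 3.6% | 7.9% | 7.9% |
| 0.3 | 2.9% | 6.4% | 7.0% |
| 0.5 | 1.8% | 4.1% | 4.5% |
| 0.7 | 0.7% | 1.7% | 1.9% |

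Results at response rate 0.5 are similar.

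**Analytic check.** Relative to what the Z-test assumes, the true variance of the difference in rates is

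V = 1 − φw + φt − φx,

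where φw, φt and φx are correlations of the yes/no responses: END with RES in one person, twin with twin in one modality, and twin with co-twin across modalities (the last two averaged over pairs, weights 31 and 14). Size = 2[1 − Φ(1.96/√V)]. For twins 0.74/0.37 at response rate 0.7, the bivariate normal gives twin correlations of the binary response of 0.516 (MZ) and 0.227 (DZ), so φt = (31 × 0.516 + 14 × 0.227)/45 = 0.426.

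- rw = 0: V = 1 + 0.426 = 1.426; size 10.1% (simulated 9.6%).
- rw = 0.5: φw = 0.318, φx = 0.191; V = 1 − 0.318 + 0.426 − 0.191 = 0.917; size 4.1% (simulated 4.1%).
- rw = 0.7: φw = 0.479, φx = 0.277; V = 1 − 0.479 + 0.426 − 0.277 = 0.670; size 1.7% (simulated 1.7%).

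**Would pairing alone repair it?** No. With correlated twins, a McNemar-type test on individuals rejects in 8.5% to 10.9% across all scenarios. A one-sample t-test on the END minus RES difference summed within each of 45 pairs rejects in 4.6% to 5.3%.

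**Mann-Whitney, MZ v DZ.** On 62 v 28 individuals, 40,000 runs each: 4.9% with no twin correlation, 10.3% at 0.60/0.38, 10.7% at 0.74/0.37 and 10.5% at 0.80/0.30. On pair means (31 v 14), with correlated twins: 4.4% to 4.7%. Analytically, the variance of the group difference inflates by 1 + r̄, with r̄ = (28 × rMZ + 62 × rDZ)/90. For 0.74/0.37, r̄ = (20.72 + 22.94)/90 = 0.485, and 2[1 − Φ(1.96/√1.485)] = 10.8%.

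**The case against.** **Objective (a) does not hang on this test alone.** A reader might infer that the Z-test decides whether response differs by modality. The article does not say so: it says that rates can be derived and compared, states no decision rule, and plans linear mixed models for the effect of the interventions on each outcome. That stands. But those models address the outcome measures, not the response rates, so the gap is softened and not closed.

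**The error may be near nominal.** That is so for an END-RES correlation of roughly 0.4 to 0.5. The observed twin correlations also come from one outcome, FMD, in small paediatric samples, and need not carry over to strength, cognition or biochemistry. The claim is therefore a range under stated assumptions, and does not say that every P-value is too small.

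**The Mann-Whitney test looks like an equal fault.** It is not. Each person contributes one value, so the only dependence is between twins; the GEE in the same sentence handles it; and a difference in level between MZ and DZ is not among the objectives or hypotheses. What remains is that *conservative* is wrong for this use, and that nothing says which result prevails.

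**The section 3.1 t-tests might be counted too.** They are presented as a descriptive first step before mixed models and GEE, so no fault is found there.

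**A paired Z-test may have been meant.** The text does not say so, and on individuals it would still ignore the twin pairs.

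**Conclusion.** The Z-test named for the response rates does not fit the design. Under the article's twin correlations, its true type I error runs from about 2% to about 13% as the assumed END-RES correlation falls from 0.7 to -0.2, against a nominal 5%. The two dependences happen to cancel only near 0.4 to 0.5. This rests on the normal latent-response model, a common response rate of 0.5 or 0.7, all 45 enrolled pairs being analysed, and the plain reading of the test as a two-sample comparison.

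This should be fixed, but it does not threaten the trial. It affects one comparison of dichotomised changes for a secondary objective that the planned mixed models also inform. The primary objective, the MZ and DZ correlations and variance components, is untouched. The wrong label on the Mann-Whitney test is a lesser point.

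**What to change.** In section 3, replace the Z-test with one of:

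- a logistic GEE for response, with modality as a within-person factor and period and order included as in section 3.1, clustered on twin pair with small-sample-corrected robust standard errors; or
- a paired or sign-flip test on the END minus RES difference at pair level, over all analysed pairs (45 enrolled, fewer if the 80% adherence rule in section 2.6 excludes some). This is simpler but leaves period and order to be handled separately.

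McNemar's test on individuals is not an adequate substitute.

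In the zygosity sentence, delete *conservative* and state that the GEE already planned there, or a rank test on pair means, carries the MZ v DZ inference. The t-tests in section 3.1 can stay as descriptive.

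The cost is about one paragraph of analysis text. No new data are needed.

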### Objectives

2.1

1.Primary objective: Assess the contribution of genetic and environmental effects on variation in cross-sectional data, and END and RES training responses, for each outcome measure2.Secondary objectives:a.Assess whether individual response to training differs between modalities for each outcome measureb.Assess whether the concordance between response to END and RES modes of training will differ between individuals

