### Hypotheses

2.2

1.The heritability of response to training will differ according to whether cross-sectional or training data are assessed.2.Response to exercise will be modality specific for each outcome measure.3.Concordance between response to END and RES modes of training will differ between individuals.4.Concordance between twins in a pair in terms of the response to END or RES modes of training will differ between MZ and DZ pairs.

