### Participant recruitment

2.3

Healthy, same-sex DZ and MZ twin pairs, between the ages of 16–40yrs, were recruited to participate in the study. Recruitment started in September 2016 and was facilitated by Twins Research Australia (formerly Australian Twin Registry [33]). Twin pairs in the Metropolitan Perth-based region were sent emails, newsletters and conventional mail regarding participation in the study. Other recruitment methods included advertising in local and Perth-based newspapers, online and social media recruiting, The University of Western Australia (UWA) email lists, flyers around UWA and nearby establishments, and word of mouth. Baseline demographic data is displayed in Table 1, and a participant flow chart in Fig. 1.

**Table 1 tbl1:** Baseline characteristics of participants enrolled in the study.

		Monozygotic (MZ)	Dizygotic (DZ)
		n = 62 (31 twin pairs, 18 F, 13 M)	n = 28 (14 twin pairs, 10 F, 4 M)
		Mean (SD)	Mean (SD)
Age (yrs)	F	24.2 (5.0)	23.8 (4.2)
	M	28.0 (5.9)	22.9 (5.3)
	Total	26.2 (6.1)	23.5 (4.5)
Height (cm)	F	170.2 (4.0)	168.6 (5.9)
	M	180.8 (4.5)	178.0 (6.6)
	Total	174.5 (6.5)	171.8 (7.5)
Weight (kg)	F	67.0 (19.6)	59.3 (9.4)
	M	81.0 (12.8)	69.1 (11.3)
	Total	74.9 (18.9)	62.6 (10.9)
BMI (kg/m^2^)	F	23.0 (6.1)	20.9 (2.8)
	M	24.7 (3.6)	21.7 (2.7)
	Total	24.4 (5.3)	21.1 (2.9)

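### Hypothesis 3 and secondary objective b are worded so that they can hardly fail, and the planned both-positive percentage is set against no chance value, so the plan states no test of within-person association between END and RES response

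*Protocol article*

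**What the plan says.** Hypothesis 3 in section 2.2 of the protocol article reads "Concordance between response to END and RES modes of training will differ between individuals". Secondary objective b in section 2.1 has the same content: "Assess whether the concordance between response to END and RES modes of training will differ between individuals". The Introduction gives the scientific question behind both, namely "whether low-response to one form of exercise training necessarily implies low-response to all modalities".

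Section 3 (Planned statistical analysis) defines a response as a single difference: "Response to training data is post minus pre for END and RES training". For the secondary objectives it then gives three items:

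- Marginal rates: "Response rates for each modality can be derived as a percentage of positive responses (>0) and compared against one another by a Z-test".
- Concordance across modalities: "Concordances can be derived as the percentage of individuals who positively respond to both exercise training modalities".
- Concordance within pairs: "within-twin pair concordances for MZ and DZ can be derived for each exercise intervention and compared to each other".

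The first and third items come with a comparison. The second, which is the one that serves hypothesis 3 and objective b, does not.

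**The concern.** There are two linked problems.

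The first is the wording. With one END change and one RES change per person, a person is either concordant or discordant. Saying that concordance differs between individuals then says only that not everyone is in the same category. For almost any outcome that will be so, whether or not the two responses are related.

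The second is the measure. The share positive on both modalities depends on how many people respond to each modality and on whether the same people respond to both. Only the latter bears on the Introduction's question. To isolate it, the observed percentage has to be set against what the two rates would give if responses were unrelated, and section 3 does not do this. The percentage also leaves out people negative on both, who are concordant too and are the group that the question about low response is about.

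The abstract lists concordance across modalities first among its example questions, and the Introduction links it to rescuing low responders by switching modality. A mix of responders that chance alone would produce could be read as informative about switching if no chance value is shown beside it.

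**Working it through.** **Is there a contrast elsewhere in the article?** The Z-test compares the two marginal rates, which is objective a and hypothesis 2. The closing comparison in section 3 is MZ against DZ, between twins and within one modality, which is hypothesis 4. The mixed models in section 3 address the effect of the interventions, and those in section 3.1 address washout, carryover and order. None relates a person's END change to the same person's RES change. The article gives no figure for cross-modality concordance to reproduce; its sample size in section 3.2 concerns rMZ against rDZ.

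**Inputs.**
- Enrolment from Table 1: 31 MZ and 14 DZ pairs, so 62 + 28 = 90 people in 45 pairs. The analysed number may be smaller because of the 80% adherence rule in section 2.6.
- Response rates: the article gives none for this trial. I assume 70% for each modality, in line with the Introduction's figure of up to 30% low response, and show 50% and 90% as a range.
- Individuals are treated as independent. As a conservative bound for twin clustering, one person per pair (n = 45) is shown as well.

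**Chance values.** With rates pE and pR and unrelated responses:
- positive on both = pE × pR = 0.7 × 0.7 = 49%
- discordant = pE(1 − pR) + pR(1 − pE) = 2 × 0.7 × 0.3 = 42%
- negative on both = 0.3 × 0.3 = 9%

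**How hard the hypothesis is to contradict.** With unrelated responses, the probability that nobody is discordant is (1 − 0.42)^90 = 5 × 10⁻²² at 70% rates and (1 − 0.18)^90 = 1.8 × 10⁻⁸ at 90% rates. With n = 45 these become 2 × 10⁻¹¹ and 1 × 10⁻⁴. There are exceptions. If 95% of people are truly positive on both, the chance that 90 people show any mix is 1 − 0.95^90 = 99.0%; at 98% it is 84%; if everyone is positive on both, it is 0.

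**What the percentage reflects** (bivariate normal changes, cut at the response rate):

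| Rates END/RES | Correlation | Both positive | Discordant | Both negative | Kappa |
|---|---|---|---|---|---|
| 50/50 | 0 | 25.0% | 50.0% | 25.0% | 0 |
| 50/50 | 1 | 50.0% | 0% | 50.0% | 1 |
| 70/70 | −1 | 40.0% | 60.0% | 0% | −0.43 |
| 70/70 | 0 | 49.0% | 42.0% | 9.0% | 0 |
| 70/70 | 0.5 | 55.7% | 28.6% | 15.7% | 0.32 |
| 70/70 | 1 | 70.0% | 0% | 30.0% | 1 |
| 90/90 | 0 | 81.0% | 18.0% | 1.0% | 0 |

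Taken alone, 49% to 50% can mean no association (70% rates) or perfect agreement (50% rates). The 50/50 row with zero correlation is also what pure noise would give.

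**Is the information there?** For people with both changes, write b for the both-positive share. Then END only = pE − b, RES only = pR − b, and neither = 1 − pE − pR + b. At 70/70 with b = 49% this gives 21%, 21% and 9%. The three planned figures therefore fix the 2x2 table.

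**Would a stated contrast work at this size?** In 20,000 simulated trials at 70/70 rates, a two-sided 5% phi test against no association rejects as follows:

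| Latent correlation | n = 90 | n = 45 |
|---|---|---|
| 0 | 4.9% | 5.0% |
| 0.3 | 41% | 24% |
| 0.5 | 85% | 56% |
| 0.8 | 99.97% | 97% |

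Using the continuous changes, the correlation detectable with 80% power (two-sided 0.05) is tanh((1.96 + 0.84)/√(n − 3)), which is 0.29 at n = 90 and 0.41 at n = 45.

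**The case against.** The strongest reply is that the data can answer the question. The planned rates and the both-positive percentage determine the table, so the chance product, kappa and phi follow by arithmetic. Once the rates are fixed, the percentage is not insensitive. At 70/70 it can only run from 40% to 70%, and moving the correlation from −0.3 to 0.6 takes it from 45.5% to 57.3%, about 39% of that range (11.8/30). Given those margins its SD at n = 90 is √(63 × 0.21 × 27/89)/90, about 2.2 points, so the step from 49.0% (no correlation) to 57.3% is nearly 4 SDs. This stands. A reader might infer that the question cannot be answered either way, and the documents do not support that.

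A reader might also infer that hypothesis 3 would be confirmed whatever the truth, with a false-positive rate near 100%. That needs a decision rule, and the article states none. There are also outcomes, with nearly everyone positive on both, where the hypothesis could fail. Nor does anything in the text say that any observed mix will be reported as support; the Introduction says only that switching could help.

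It can further be said that this is a secondary objective in a condensed article, phrased permissively, with a supplementary figure and possibly an analysis plan not shown, and that a descriptive percentage is a legitimate summary. That lowers the weight but does not remove the point. The article itself words the hypothesis and fixes the measure, gives the neighbouring measures a comparison, and cites the figure only for deriving the percentage. A separate analysis plan would inherit a hypothesis that can hardly fail.

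**Conclusion.** The point holds in a limited form. Hypothesis 3 and objective b are practically irrefutable as worded, and the one measure assigned to them is reported without the chance value that would make it interpretable. At assumed rates of 70% and unrelated responses, that chance value is 49% positive on both, with 42% discordant. The defect is a missing contrast, not missing data.

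The figures rest on assumed response rates, a bivariate normal model for the correlated cases, and individuals treated as independent, with n = 45 as the bound for clustering. The conclusion does not depend on the particular rates or on where the responder cut-off is placed. It concerns a secondary objective and leaves the primary heritability analysis untouched, but it should be put right because it bears on one of the trial's headline questions.

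**What to change.** Restate hypothesis 3 and objective b as an association across individuals between the END change and the RES change, with no association as the null. For each outcome, estimate the END-RES change correlation with its 95% CI from a model that allows for twin pairs and for order. Keep the concordance percentage as a description, shown in the full 2x2 table (both, END only, RES only, neither) beside the counts expected from the product of the two response rates.

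State the limit as well. Because each modality has a single post-minus-pre change, a correlation near zero cannot tell unrelated true responses from measurement error.

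The cost is rewording one hypothesis, one objective and the matching analysis paragraph, plus one extra model per outcome on data already collected. Hypothesis 3 may then fail, which it hardly can at present.
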